#### Recruitment and sample selection

Potential participants will first be screened by nurses based on inclusion and exclusion criteria and informed about the study during a consultation with nurses if they meet the inclusion criteria. To assess the external validity of the recruited sample of participants, age and gender will be collected for those participants who refuse to participate in the study [18]. If potential participants are interested in participating in this study, their names will be placed on a trial list. The investigator will contact the participants and explain the procedure. If the participants agree, an informed consent form will be sent. If the participants have any questions, they can contact the investigator.

Upon receipt of the signed informed consent form, the participants will be registered in the electronic case report form (eCRF), and the basic information will be recorded at baseline. Then, the doctor will assess the neuroelectrophysiology data, and the ability to perform ADLs and motor function will be evaluated by an occupational therapist. The participants received a reminder or were contacted by phone at subsequent testing time points. Measurements are recorded by the nurse specialist in the Electronic Patient Record.

After recruitment, individuals with SCI will be measured at disease durations of 1 month, 2 months, 4 months, 6 months and 12 months, including single pulse TMS (spTMS) to evaluate the CSE in bilateral M1 hand areas, ppTMS to evaluate the intracortical excitability in bilateral M1 hand areas, and fNIRS to evaluate bilateral M1 hand area blood flow. All subjects will receive an assessment scale. The matched healthy controls will be measured during the same period after recruitment (flow chart, Table 1).

**Table 1 Tab1:** SPIRIT-figure of the measurement instruments and time of assessment

		Study period						
		Enrolment						
Timepoint	Type	Healthy control	1 month (SCI-T1)		2 months (Control/SCI-T2)	4 months (Control/SCI-T3)	6 months (Control/SCI-T4)	12 months (Control/SCI-T5)
**Enrolment**								
Eligibility screen		**×**	**×**					
Informed consent		**×**	**×**					
**Assessments**								
spTMS (RMT, MEP)	Neuroexcitability	**×**	**×**		**×**	**×**	**×**	**×**
ppTMS (SICI, ICF, LICI)	Neuroexcitability	**×**	**×**		**×**	**×**	**×**	**×**
fNIRS	Neuroexcitability	**×**	**×**		**×**	**×**	**×**	**×**
**Prognostic evaluation**								
Motor Score	Motor Function	**×**	**×**		**×**	**×**	**×**	**×**
MAS	Motor Function	**×**	**×**		**×**	**×**	**×**	**×**
AIS Grade	Injury Extent	**×**	**×**		**×**	**×**	**×**	**×**
SCIM	ADL ability	**×**	**×**		**×**	**×**	**×**	**×**
MBI	ADL ability	**×**	**×**		**×**	**×**	**×**	**×**
**Basic characteristic**								
Age	Basic Characteristic	**×**	**×**					
Gender	Basic Characteristic	**×**	**×**					
Height, Weight	Basic Characteristic	**×**	**×**					
Education	Basic Characteristic	**×**	**×**					

*Abbreviations* SCI: spinal cord injury; spTMS: single pulse TMS; ppTMS: paired-pulse TMS; fNIRS: functional near-infrared spectroscopy; RMT: resting motor threshold; MEP: motor evoked potentials; SICI: short-interval intracortical inhibition; ICF: intracortical facilitation; LICI: long-interval intracortical inhibition; AIS: American Spinal Injury Association (ASIA) impairment scale; AIS: MAS: modified Ashworth scale; MBI: modified Barthel index; SCIM: spinal cord independence measure

**Flow chart Figa:**
[figure not shown]
Flow diagram of the study design. *Abbreviations* SCI: spinal cord injury; spTMS: single pulse TMS; ppTMS: paired-pulse TMS; fNIRS: functional near-infrared spectroscopy; MS: motor score; AIS: American Spinal Injury Association (ASIA) impairment scale; MAS: modified Ashworth scale; MBI: modified Barthel index; SCIM: spinal cord independence measure

Every participant data file will be given a number and stored in a secure and accessible place. The files will be kept for three years after completion of the study.

### Outcome measures

#### Primary outcome

##### spTMS

To evaluate the changes in the M1 hand area CSE between individuals with SCI and healthy controls, the amplitude of the MEP and the resting motor threshold (RMT) will be detected through spTMS equipment (MEP-9404 C, Japan).

The MEP of the M1 hand area was recorded by the magnetic stimulation coil placed in the M1 hand area on the left side of the skull. The recording surface Ag-AgCl electrode and reference electrode were pasted on the abdomen of the abductor pollicis brevis muscle of the right hand and connected to the recording equipment. A single-pulse TMS is delivered to the hotspot under 80% of the maximum stimulator output. The MEP latency and amplitude of the abductor pollicis brevis muscle were recorded. RMT is defined as the minimal amount of stimulus intensity producing MEP peak-to-peak ≥ 50 µV in at least 5 out of 10 consecutive tracks [19]. The protocol used for the right M1 hand area was the same as that described above (Fig. 1A).

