### Participants

#### Inclusion and exclusion criteria

The inclusion criteria for individuals with SCI were as follows: (a) 18–75 years old, right-hand dominant (Edinburgh Handedness Inventory); (b) diagnosed with SCI [15]; (c) stable MEP in the M1 hand area was detectable; (d) no cognitive impairment (Mini-Mental State Examination score ≥ 24) [16]; (e) disease course ≤ 1 month (from SCI onset to first assessment); and (f) agreed to participate in this study and signed the informed consent form. Exclusion criteria: (a) serious nervous system disease, unable to tolerate relevant tests; (b) upper limb fracture, arteriovenous fistula or other diseases leading to movement disorder; (c) ferromagnetic implants in the head or neck; (d) implantation of a cardiac pacemaker; (e) severe coagulation disorder, severe cardiac insufficiency or uncontrollable hypertension: systolic blood pressure > 160 mmHg or diastolic blood pressure > 100 mmHg; (f) other serious systemic diseases such as tumors; (g) taking drugs that may affect the TMS examination within a week, including baclofen, diazepam and other drugs [17]; (h) absolute contraindications for TMS examination.

The inclusion criteria for healthy controls were as follows: (a) 18–75 years old, right-hand dominant (Edinburgh Handedness Inventory); and (b) stable MEPs. Exclusion criteria included the above situations in which TMS could not be performed.

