#### Motor score (MS)

The MS mainly evaluates the strength of key muscles innervated by different spinal nerves. The total score is 100, consisting of the upper extremity MS (UEMS) and lower extremity MS (LEMS) (Supplemental Table 1).

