#### MEP and hemispheric excitability conversion degree

The MEP amplitudes of patients and controls will be analyzed by nonparametric tests. The MEP latency and central motor conduction time (CMCT) are analyzed with independent samples *t* tests. The hemispheric excitability conversion degree [ln(DH/NDH ratio)] [13] is compared with generalized estimating equations (GEEs) [27] with respect to disease course (1 m, 2 m, 4 m, 6 m, and 12 m). **P* < 0.05 was regarded as a significant difference.

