#### Correlation analysis and multiple linear regression analysis

Correlation analysis of hemispheric excitability conversion degree and overall functional recovery was performed to determine the effects of disease course, AIS grade, and neurological level of injury. Pearson correlations between different phases/groups were calculated after the normality test. **P* < 0.05 is regarded as a significant difference.

Univariate and multivariate linear regression analyses will be conducted to validate the influence of hemispheric excitability conversion degree as an independent factor. The MBI and SCIM are set as the linear regression analysis outcomes. The inclusion criterion for univariate analysis was *P* < 0.10. **P* < 0.05 is regarded as a significant difference.

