Based on our previous retrospective research, a correlation analysis of hemispheric excitability conversion degree and overall functional recovery was performed to investigate the effects of neurological level of injury, disease course and AIS grade. The results showed a completely different correlation tendency in patients in the SCI subgroup. Among patients with different degrees of neurological injury, patients in the noncervical injury group had a significantly positive correlation with the degree of hemispheric CSE conversion and ability to perform ADL ability, while a nonsignificant positive correlation was found in the cervical injury group. This finding may be due to the influence of cervical injury on the UE CST pathway. In patients with AIS A, the degree of hemispheric CSE conversion was significantly positively correlated with the ability to perform ADLs, while no correlation was observed in AIS non-A patients. We further observed and confirmed changes in the cortical excitability of the M1 hand area under different influencing factors over a long period of time through a prospective cohort study.

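### ln(DH/NDH) is a right-thumb to left-thumb response ratio, and no modifier named in the analysis separates right-left cord or root damage from M1 asymmetry in pooled and cervical analyses

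*Protocol article*

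**What the plan says.** Under Primary outcome, spTMS, the left M1 hand area is stimulated with the recording electrodes "pasted on the abdomen of the abductor pollicis brevis muscle of the right hand and connected to the recording equipment". For the other hemisphere, "The protocol used for the right M1 hand area was the same as that described above", which implies recording from the left thumb muscle. Intensity is fixed rather than scaled to each side's threshold: "A single-pulse TMS is delivered to the hotspot under 80% of the maximum stimulator output".

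The inclusion criteria require right-handedness in both groups. They admit SCI at any level if a stable hand MEP can be detected, and set no condition on right-left symmetry. Upper limb fracture and some other causes of movement disorder are excluded.

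In the section on MEP and conversion degree, ln(DH/NDH) is compared over disease course by GEE. In the correlation and regression section, its relation to functional recovery is examined by disease course, AIS grade and neurological level. It is then tested as an independent factor: "The MBI and SCIM are set as the linear regression analysis outcomes". Regression candidates are not listed; entry is by a univariate P < 0.10 screen.

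The motor score, which includes an upper-extremity part (UEMS), is taken at every visit (Table 1), but the statistical section does not name it. The Discussion values UEMS only for telling arm from leg function. On the weaker correlation in cervical patients in the earlier study it says: "This finding may be due to the influence of cervical injury on the UE CST pathway".

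**The concern.** An MEP amplitude depends on the whole path from cortex through cord and root to muscle. A ratio of two such responses cancels damage that is equal on both sides, but not damage that differs between them. In a cervical injury, unequal damage is part of the condition under study, so arm-disease exclusions do not remove it.

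A right-sided deficit lowers ln(DH/NDH). If it also lowers dominant-hand self-care, it lowers MBI and SCIM. Together these reproduce the pattern the Introduction expects (an index further from healthy controls, with worse ADL) without any change in M1. The protocol intends the result to inform rTMS parameters and brain-computer interface design, so taking a spinal asymmetry for a cortical one would matter.

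**Working it through.** **1. The plan's own figure.** The plan gives no figure for this point. Its sample size reproduces and is not in dispute: with P1 = 0.70, P2 = 0.26, two-sided α = 0.05 and 90% power, n = [1.96·√(2·0.48·0.52) + 1.2816·√(0.70·0.30 + 0.26·0.74)]² / 0.44² = (1.385 + 0.813)² / 0.1936 = 24.95, so 25 per group; 25 × 1.2 = 30.

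**2. What the index contains.** Right-handedness makes DH the left M1, recorded at the right thumb; NDH is the right M1, recorded at the left thumb. Let C be cortical asymmetry and R and L the log transmission of the right and left pathways. Then ln(DH/NDH) = C + (R − L).
- Equal damage: R = L, no shift.
- Right response halved, left intact: ln(0.5) = −0.69.
- Two patients with the same level, AIS grade and disease course, one with the right response halved and one with the left, differ by 0.69 − (−0.69) = ln 4 = 1.39. The named modifiers are identical for both.

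**3. Effect on the ADL association (illustration; no input is from the documents).** Simulation with 25 SCI patients, 2,000 runs, C with SD 1 and no effect on ADL, side damage only in cervical patients, and left-side damage weighted 0.3 against the right in ADL. False-positive rates for the index at nominal 5% (simulation error about ±1 point):

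| Cervical share | SD of side damage | ADL effect of right side | Mean r | Unadjusted | + level | + level, summed arm score | + level, each arm separately |
|---|---|---|---|---|---|---|---|
| 30% | 0.5 | 0.5 | 0.02 | 5.8% | 5.4% | 5.7% | 5.9% |
| 30% | 0.5 | 1 | 0.04 | 6.6% | 7.4% | 6.6% | 5.5% |
| 30% | 1 | 0.5 | 0.08 | 8.0% | 7.6% | 6.8% | 5.2% |
| 30% | 1 | 1 | 0.14 | 12.5% | 12.8% | 12.1% | 4.7% |
| 60% | 0.5 | 0.5 | 0.05 | 5.3% | 5.3% | 5.3% | 4.2% |
| 60% | 0.5 | 1 | 0.09 | 7.8% | 8.7% | 7.8% | 5.1% |
| 60% | 1 | 0.5 | 0.13 | 11.6% | 11.9% | 11.4% | 4.8% |
| 60% | 1 | 1 | 0.21 | 19.3% | 19.7% | 23.5% | 4.9% |

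With no side damage the rate is 4-5%. A level term or summed arm score does not remove the inflation; side-specific scores do. Given R − L, what remains of the index is C, so the difference alone suffices. The simulated scores measure side damage without error, so this is the best case.

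A second set of assumptions (n = 30, SD 4 points per side, 0.2-0.3 log units per point, dominant-hand weight 0.75-0.9) gives 7-15% with 50-70% cervical and 11-23% if all are cervical. A weight of 0.6 gives 5-7%. Noise in the ADL score also matters: with 50% cervical, weight 0.75 and slope 0.2, a residual ADL SD of 5, 10 or 15 gives 9%, 5.5% and 5.5%; slope 0.1 gives 5-6% throughout.

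**4. Precision.** Assume 0.2 log units per point, a right-left SD of 5, cortical SD 1 and 50-70% cervical. The added variance is 0.5 to 0.7 × (0.2 × 5)² = 0.5 to 0.7. A true r of 0.50 becomes 0.50/√1.5 = 0.41 or 0.50/√1.7 = 0.38 if the added part is unrelated to ADL. Fisher-z power at n = 30 falls from 81% to 62% or 56%.

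**5. What it cannot explain.** Start from 27% of people with NDH above DH (normal log ratio, SD 1). Add random side damage of SD 4 points per side in 60% of patients at slopes of 0.1-0.3: the share rises to 29-33%. The sample size section gives about 70% in SCI. Damage with no preferred side can only move the share toward 50%.

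**The case against.** Much of the case on the other side stands.

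- A reader might infer that the arm score is never used. The article does not support that: it lists no regression candidates, UEMS could be among them, and a fuller plan may say so. What can be said is that UEMS is not named, and that a univariate screen would not guarantee a right-left term a place.
- A reader might infer that analysis by neurological level gives no protection. That is true of a level term in a pooled model and within cervical patients. It is not true of the noncervical stratum, where cord damage to the hand pathway is largely absent and which the plan already provides for.
- A reader might infer that this mechanism explains the earlier findings. It does not: the Discussion reports the significant ADL correlation in noncervical patients and a nonsignificant one in cervical patients, the reverse of what it predicts. Step 5 shows that it does not produce the group shift either.
- The size is assumed, and several plausible settings give almost no inflation. The all-cervical figures at n = 30 overstate what a smaller cervical subgroup would show.
- ppTMS is expressed relative to a baseline MEP and fNIRS is not a muscle response, so both could support a cortical reading. The plan does not tie either to the conversion degree.
- Arm strength is itself an output of the corticospinal system, so adjusting for it may remove part of a real cortical effect. This argues for reporting both coefficients, not for omitting the adjusted one.

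The Clinical and research implications section concedes uncontrollable influences. A right-left difference is probably already measured, so that caveat does not cover it.

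**Conclusion.** The point holds in limited form. As described, ln(DH/NDH) is a two-muscle ratio, and no modifier named for the GEE or the correlation analysis encodes side. Pooled and cervical results therefore cannot separate a right-left difference in cord or root damage from M1 asymmetry. Bias toward the hypothesis further requires that dominant-hand weakness lowers MBI and SCIM, which is reasonable but not stated in the documents. Its size is unknown: illustrative false-positive rates run from about 5% to about 20%, on inputs that are all assumptions. The documents do not support concluding that the planned analysis is invalid, that the noncervical result is compromised, or that the earlier cross-sectional findings are an artefact of this kind.

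**What to change.** Keep the planned models and add a prespecified sensitivity analysis to the two statistical sections concerned:

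1. Report the ln(DH/NDH) coefficient for MBI and for SCIM with and without the same-visit right-minus-left UEMS. Do the same for the disease-course terms in the GEE. Total UEMS is not a substitute.
2. Name the noncervical analysis, or one in patients with full arm scores on both sides, as the one that supports an M1 interpretation.
3. Describe pooled or cervical results as corticospinal asymmetry unless the association persists in that analysis.

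The cost is one degree of freedom and no new visits, provided that the motor score sheet (Supplemental Table 1, not shown) records each side. Over-adjustment is possible if cortical asymmetry acts through hand strength, which is why both coefficients are reported. The noncervical group will be small: if 50-70% of 30 patients are cervical, it has 15 to 9 patients before dropout. At n = 15, power for r = 0.50 is about 48% (0.549 × √12 = 1.90; 1.90 − 1.96 = −0.06). A nonsignificant result there should therefore be reported with its confidence interval and not read as absence of an M1 effect.

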**Fig. 1 Fig1:**
[figure not shown]
Bilateral M1 hand area excitability measurement and fNIRS measurement. **A**. spTMS; **B**. ppTMS; **C**. fNIRS measurement; **D**. fNIRS channel layout and ROI; **E**. Handgrip task design. During the test, the subjects were required to perform the grip experiment, which included the following steps: 1) left-hand clenching for 5 seconds, releasing for 5 seconds, and repeated three times; 2) 15 s resting state; and 3) right-hand clenching for 5 seconds, releasing for 5 seconds, and repeated three times. *Abbreviations* spTMS: single pulse TMS; ppTMS: paired-pulse TMS; fNIRS: functional near-infrared spectroscopy

##### ppTMS

To evaluate the changes in intracortical excitability of the M1 hand area between individuals with SCI and healthy controls, the amplitude of ppTMS (Neurosoft, Russia) will be measured.

During the measurements, TMS was applied twice over the M1 area. The first pulse is defined as the conditional stimulus, and the second pulse is defined as the test stimulus. By determining the change in the test stimulus relative to the baseline MEP, the excitability or inhibitory state of the M1 hand area can be noninvasively measured. The inhibitory indicators included short-interval intracortical inhibition (SICI, pulse interval 2.5 ms) and long-interval intracortical inhibition (LICI, pulse interval 100 ms). The commonly used excitability indicator is intracortical facilitation (ICF, pulse interval 12 ms). Previous studies have confirmed that ICF is related to N-methyl-D-aspartic acid (NMDA) receptor function, while SICI and LICI are related to gamma-aminobutyric acid A (GABA_A_) and gamma-aminobutyric acid B (GABA_B_) receptor function, respectively [20] (Fig. 1B).

#### Secondary outcomes

Based on the theory of neurovascular coupling (NVC), which states that increased neural activity can drive changes in local blood flow through neurovascular coupling [21], we utilized fNIRS (NirSmart, HuiChuang, China) to evaluate changes in blood flow in the M1 area between individuals with SCI and healthy controls.

The fNIRS test method parameters have been previously described [19]. The near-infrared electrode cap can detect near-infrared light absorption at 780, 805 and 830 nm, and the data can be converted into oxygenated hemoglobin (HbO), deoxyhemoglobin (HbR) and total hemoglobin (HbT) values. The detection channels were located according to Montreal Neurological Institute (MNI) coordinates, and the regions of interest (ROIs) were the bilateral M1, primary sensory cortex (S1), premotor cortex (PMC) and prefrontal cortex (PFC) (Fig. 1C D). During the test, the subjects were required to perform the grip experiment [19], which included (1) clenching the left hand for 5 s, releasing for 5 s, and repeating the process three times; (2) resting for 15 s; and (3) clenching the right hand for 5 s, releasing for 5 s, and repeating the process three times (Fig. 1E).

### Overall functional recovery evaluation

To evaluate the overall functional recovery of individuals with SCI, we utilized different scales and assessments for motor function and ADL ability evaluation.

#### Motor score (MS)

The MS mainly evaluates the strength of key muscles innervated by different spinal nerves. The total score is 100, consisting of the upper extremity MS (UEMS) and lower extremity MS (LEMS) (Supplemental Table 1).

#### Modified ashworth scale (MAS)

The MAS is the most commonly used clinical scale for measuring muscle tone [22]. The classification standards included 0, 1, 1+, 2, 3, and 4. (Supplemental Table 2).

#### ASIA impairment scale (AIS) grade

The AIS grade [23] mainly determines the degree of SCI (complete/incomplete injury) and can be divided into five scales: A, B, C, D and E. A indicates complete injury, B-D indicates incomplete injury, the degree of injury decreases successively, and E indicates normal sensorimotor function (Supplemental Table 3).

#### Spinal cord independence measure (SCIM)

The SCIM mainly evaluates the prognosis and overall quality of life of individuals with SCI [24]. The total score is 100. There are 17 items in total, of which Item 12 (**SCIM12**) is of particularly important for the evaluation of motor function in individuals with SCI [25]. The total SCIM12 is 8 (Supplemental Table 4).

#### Modified barthel index (MBI)

The MBI [26] mainly evaluates the independent living ability of individuals with SCI and includes 10 items. Compared with SCIM, the MBI focuses on patients’ self-care ability in daily life, which indicates whether patients can operate independently when completing the above actions. The total score is 100 (Supplemental Table 5).

### Data management

All recorded data will be collected in the CRF paper form. One authorized clinical staff member will enter the data into the eCRF. The entered data will be subjected to plausibility, monitoring and medical review. Implausible or missing data will be queried.

### Statistical analysis

#### Descriptive statistics

The data will be analyzed descriptively and divided into SCI and control groups. Measurement or enumeration data are presented as the mean ± SEM (standard error of the mean) or number [%] (N[%]), respectively. *T tests, chi-squared tests* or *Fisher’s exact* tests were utilized for data comparisons. **P <* 0.05 is regarded as a significant difference.

